#### **4.7.4.4. Urinalysis**

Urine sampling and urinalysis will be performed using standard procedures. Urinalysis includes testing of the general urine properties (color, clarity, specific gravity, pH, protein, glucose) and urinary sediment microscopy (epithelium, erythrocytes, leukocytes, cylinders, bacteria, salts).

##### ***Frequency and timing:***

Urine samples will be taken at screening, at Week 24, and Week 55. Urinalysis should be performed with the mid-stream sample of the first morning urine.

#### **4.7.5. ECG**

A 12-lead ECG is recorded according to the standard procedure.

##### ***Frequency and timing:***

ECG will be performed at screening, at Week 24, and Week 55.

#### 4.7.6. Tests for tuberculosis

In this study, results of the Diaskintest® or QuantiFERON or T-Spot.TB assays obtained with standard procedures will be accepted. Only Diaskintest® or QuantiFERON or T-Spot.TB test results obtained at screening will be accepted for the screening purpose. The Diaskintest® or QuantiFERON or T-Spot.TB test and the test interpretation should be performed by a certified healthcare professional.

Diaskintest® is an intra-skin diagnostic test with a recombinant protein containing two antigens (ESAT6 and CFP10) of *Micobacterium tuberculosis* and *Micobacterium bovis*, virulent strains of mycobacteria. The procedure and of Diaskintest® and results assessment are similar to those of the Mantoux test (PPD-L). The test is done with a thin needle, intradermally, into the middle third of the antebrachium. After 72 hours, the physician or nurse evaluates the response by measuring the transverse (with reference to the brachium axis) size of hyperemia and infiltrate (papula) in mm with a transparent ruler. Hyperemia is taken into account only if no infiltrate is seen. The following responses for the test can be seen (source [http://www.diaskintest.ru/page\\_2.html](http://www.diaskintest.ru/page_2.html)):

- Negative: no infiltrate or hyperemia. A “prick reaction” of up to 2 mm may occur.
- Indeterminant: hyperemia with no infiltrate.
- Positive: an infiltrate (papula) of any size.

The QuantiFERON test allows evaluating plasma levels of the specific gamma interferon to confirm or exclude the tuberculosis infection.

Procedure of the QuantiFERON test is as follows:

Blood should be collected in the morning. Patients must be fasting (at least 8 hours after the last food intake). Blood samples will be collected into three vacuum test tubes from a QuantiFERON Assay Kit (positive control, negative control, test), with 1 mL of blood transferred in each tube. Remove the tube from the syringe 2 to 3 sec after the blood has reached a black mark on the edge of the label (a measure showing 1 mL of blood). If the blood does not reach the mark, take a new blood sample. The tubes with the blood must be kept at room temperature (+17 °C to +25 °C). Do not refrigerate or freeze the blood samples. Start incubating the tubes within 10 hours after the blood was collected.

Shake well the tubes after blood sampling. **NB! Shake each tube 10 times for 5 seconds so that the internal surface of the tube is coated with blood.**

Incubate the tubes for 16-24 h in a vertical position at 37 °C. During the incubation, lymphocytes recognize mycobacterial antigens. This recognition process includes the production of gamma interferon. If the tubes are not incubated shortly after blood collection, shake them again 10 times before incubation. If the tubes are shaken well, blood foams. This does not affect the test results

and must be seen if the assay is correct. Document the start and end of the incubation in the *BCD-057-2 Incubation Log*, which is attached to the Investigator's Guide provided by the Central Laboratory.

When the incubation is complete, spin the tubes in a centrifuge at 2000-3000 g for 15 min. After spinning, plasma should be clear and red (but not dark red). If plasma does not look correct, re-spin the tubes in the centrifuge at a higher rate.

Before the delivery service arrives, store the tubes chilled in a bag labeled "QuantiFERON Assay Tubes Kit" (+2...+8 °C).

The biospecimens must be sent to the Central Laboratory on the day when the incubation is completed. The tubes must be shipped in a vertical position.

The Central Laboratory uses ELISA assay to test plasma for gamma interferon, which is formed as an immune response to the antigens.

Use only tubes from the QuantiFERON Assay Kit for the QuantiFERON test because each of its tube contains a specific antigen. Do not use any tubes of the same colors but not from the QuantiFERON Assay Kit.

Interpretation of QuantiFERON test results. There are three possible results: Positive, negative, and indeterminant. Indeterminant results may occur due to the sensitivity to the tuberculosis antigen.

The T-Spot.TB is an immunobiologic diagnostic test for tuberculosis. It is based on counting the T cells that have been specifically activated by *Mycobacterium tuberculosis*.

The patient must be fasting before providing a blood sample for T-Spot.TB test. The sample should be collected in sodium or lithium heparin.

Volume of blood drawn: at least 6 mL.

Rotate the tube upside down 3-4 times immediately after sampling. Do not shake the tube and avoid foaming.

Before delivered to the laboratory for testing, blood samples (no preservatives added) can be stored for not more than 30 hours in a vertical position at a temperature from 18°C to 25°C. Do not refrigerate or freeze the biospecimens.

Patients with indeterminant and/or positive results of the QuantiFERON/Diaskintest® are allowed in the study only if all of the following three criteria are met:

- The patient tested negative in one additional QuantiFERON assay.
- No signs of active tuberculosis are seen on the chest X-ray (or fluorography/CT/MRI) done any time within 1 month before signing the informed consent form.
- The TB specialist's report that the patient has no tuberculosis; the report should be given during the screening period.

The patient who has indeterminant or positive results of the QuantiFERON assay or T-Spot.TB test or Diaskintest® at Week 25 is allowed to continue the study only if all three requirements are met:

- The patient tests negative in one additional QuantiFERON assay.
- The chest X-ray shows no signs of active tuberculosis.
- The TB specialist confirms that the patient has no tuberculosis.

Otherwise, the patient has to be removed from the study.

***Frequency and timing:***

The test will be performed at screening, at Week 25, and at Week 55.

***4.7.7. Chest x-ray and fluorography***

Chest X-ray is performed to rule out pulmonary tuberculosis. The examination is conducted according to the site's standard procedure. Images are taken in the front view. If necessary, the Sponsor's representative may request the images (if the subject develops active TB while in the study).

***Frequency and timing:***

The test will be performed at screening, at Week 25, and at Week 55. At screening, fluorography may be done instead of the chest X-ray. Screening chest X-ray is not required if the patient has results of the chest X-ray or fluorography or CT or MRI performed within 1 month before signing the informed consent form.

***4.7.8. PASI and BSA assessment***

The **PASI** allows evaluating the extent and severity of skin symptoms of psoriasis. Table 15 presents the worksheet used for PASI scoring.

**Table 21. Psoriasis area and severity index (PASI). Lesion score: 0 - no symptoms; 1 – mild; 2 – moderate; 3 – severe; 4 – very severe**

| 1 |            | Head and neck | Trunk | Upper limbs | Lower limbs |
|---|------------|---------------|-------|-------------|-------------|
|   | Erythema   | 0             | 0     | 0           | 0           |
|   |            | 1             | 1     | 1           | 1           |
|   |            | 2             | 2     | 2           | 2           |
|   |            | 3             | 3     | 3           | 3           |
|   |            | 4             | 4     | 4           | 4           |
| 2 |            | Head and neck | Trunk | Upper limbs | Lower limbs |
|   | Induration | 0             | 0     | 0           | 0           |
|   |            | 1             | 1     | 1           | 1           |
|   |            | 2             | 2     | 2           | 2           |
|   |            | 3             | 3     | 3           | 3           |
|   |            | 4             | 4     | 4           | 4           |

|   |         |                  |       |             |             |
|---|---------|------------------|-------|-------------|-------------|
| 3 |         | Head
and neck | Trunk | Upper limbs | Lower limbs |
|   | Scaling | 0                | 0     | 0           | 0           |
|   |         | 1                | 1     | 1           | 1           |
|   |         | 2                | 2     | 2           | 2           |
|   |         | 3                | 3     | 3           | 3           |
|   |         | 4                | 4     | 4           | 4           |
| 4 | Total   |                  |       |             |             |

**Table 22. Percentage area affected, %**

|                                                                       |                                                                                                                                                    |      |      |      |      |
|-----------------------------------------------------------------------|----------------------------------------------------------------------------------------------------------------------------------------------------|------|------|------|------|
| 5                                                                     | 0 refers to no symptoms; 1 is < 10%; 2 is from 10% to 29%; 3 is from 30% to 49%; 4 is from 50% to 69%; 5 is from 70% to 89%; 6 is from 90% to 100% |      |      |      |      |
| 6                                                                     | Area score                                                                                                                                         |      |      |      |      |
| 7                                                                     | Multiply the value in line 4 by the value in line 6                                                                                                |      |      |      |      |
| 8                                                                     | Body surface area                                                                                                                                  | ×0.1 | ×0.3 | ×0.2 | ×0.4 |
| 9                                                                     | Multiply the value in line 7 by the value in line 8                                                                                                |      |      |      |      |
| Total value
(add together each of the scores for each body region) |                                                                                                                                                    |      |      |      |      |

Each symptom (erythema, induration, and scaling) is assessed with a 4-point scale from 0 (none) to 4 (very severe), separately for the skin of the head and neck, body, upper and lower limbs (lines 1-3). The assessment was performed for the area mostly affected by the evaluated symptom. The scores were summarized (line 4).

The BSA affected by psoriasis is then estimated for each anatomical region. The BSA is estimated with the palm method. One percent of BSA is approximately equal to the palm of the patient's hand excluding fingers. It is assumed that the skin of the head and neck corresponds to 10% of all skin area, trunk – to 30%, upper limbs – to 20%, and lower limbs – to 40%. Thus, one palm makes up 10% of the scalp skin, 3.3% of trunk skin, 5% of the skin of the upper limbs, and 2.5% of the skin of the lower limbs.

To estimate the BSA score for each section, the affected area (%) from each section is matched to the values from line 5, and the score was entered to line 6.

After that, the value in line 7 is multiplied by the weight of the respective section (0.1 for the head, 0.2 for upper limbs, 0.3 for the trunk, and 0.4 for the lower limbs).

The values in line 9 are then summed up to obtain the PASI score, which can vary from 0 (no rashes) to 72 (the most severe psoriatic process).

The PASI score is calculated automatically when the investigator enters the following data in the eCRF: severity of erythema, induration, and scaling by sections and the BSA. The total PASI score and severity of individual symptoms by anatomical regions (lines 1-4 of Table 15) must be recorded in source documents

The investigator determines the BSA during the study visits and records it in source documents and eCRF as a total body surface affected by psoriasis (%). Assessment is performed with the “palm” method.

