## **7. Efficacy evaluation**

### **7.1. List of efficacy variables**

#### **7.1.1. Definition of variables**

The efficacy will be assessed based on the indicators of the disease activity and patient's general health.

The PASI is a commonly used tool to assess the area and severity of psoriasis in clinical trials. The PASI score is an integral value from 0 (no symptoms) to 72 (the most severe psoriatic process). It shows the area affected by psoriasis (on the head, legs, arms, and trunk) and includes the severity of erythema, scaling, and induration. There are several modifications of PASI scoring, but the most conventional one is a scale considering all the three signs given above. The information value of the method decreases if the body surface area affected by psoriasis is too small.

The PGA scale is another common tool used to assess the severity of psoriasis. The scale includes 5, 6, or 7 items that the investigator uses to assess the severity of the disease. In most versions of the PGA scale, the morphology of plaques and the area of skin affected by psoriasis are not taken into account. This makes the assessment rather intuitive. The PGA score 0 refers to no signs of psoriasis, while the maximum score refers to the highest disease severity. This scale has several modifications, and the sPGA (static PGA) is the most commonly used one. The sPGA scale allows assessing psoriasis signs at a certain time point. The dPGA (dynamic PGA) scale can be also used in clinical studies. However, when using the dPGA, the physician should remember how he/she assessed the severity of psoriasis during the previous assessment, and this is not always possible. This study uses the sPGA scale consisting of 5 questions.

The body surface area (BSA) affected by psoriasis is another conventional endpoint used in clinical studies. This measure allows an objective assessment of the extent of psoriasis.

This study also evaluates the health-related quality of life. The SF-36 is a standard validated and commonly used questionnaire to assess this parameter. The DLQI questionnaire allows specifically assessing the quality of life in patients with skin diseases.

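### PASI takes each sign's severity from the area worst affected by that sign but multiplies it by all affected skin in the region, so the severity does not describe the area it weights

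*Protocol*

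**What the plan says.** Section 4.7.8 (Tables 21 and 22) builds PASI in four regions.

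- **Severity.** Each of three signs is graded from 0 to 4 per region, and the place to look is stated: "The assessment was performed for the area mostly affected by the evaluated symptom". The instruction is specific to the sign, so three different spots may supply the three grades. They are added in line 4.
- **Area.** "The BSA affected by psoriasis is then estimated for each anatomical region", and "the affected area (%) from each section is matched to the values from line 5, and the score was entered to line 6". This counts all affected skin in the region.
- **Product.** Line 7: "Multiply the value in line 4 by the value in line 6". The region weights are "0.1 for the head, 0.2 for upper limbs, 0.3 for the trunk, and 0.4 for the lower limbs", and the weighted products are summed.

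Section 7.1.1 describes the resulting score this way: "It shows the area affected by psoriasis (on the head, legs, arms, and trunk) and includes the severity of erythema, scaling, and induration". Nowhere does the protocol ask for an average or representative severity.

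PASI defines the primary endpoint (PASI 75 at Week 16, section 4.1.1), one of the three severity limits for entry (PASI of at least 12, section 5.1) and a stratification factor (below 20, or 20 and above, section 4.2).

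**The concern.** A product of severity and area makes sense when the severity describes the area it multiplies. Under section 4.7.8 the whole affected area of a region is counted as if it were as bad as its worst place for each sign. A region with mixed lesions and a region that is uniformly severe can receive the same score.

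At stake are the PASI entry limit, the PASI stratum and the 75% threshold of the primary endpoint, all of which are read from this score. There is also a question of consistency. This is a multicentre trial. If some raters follow the sentence and others average over lesions, the score will mean different things at different sites.

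**Working it through.** **Formula.** PASI = sum over regions of weight × (erythema + induration + scaling) × area score, with weights 0.1 (head and neck), 0.3 (trunk), 0.2 (upper limbs) and 0.4 (lower limbs).

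**Check against the protocol's own figure.** All signs 4 and all area scores 6: 12 × 6 × (0.1 + 0.3 + 0.2 + 0.4) = 72, the stated maximum.

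**Direction.** The maximum over lesions is never below their average, and the area score is the same under both rules. Worst-area PASI is therefore never lower than representative PASI. It is higher whenever lesions in a region differ by enough to move a whole-number grade. If lesions are uniform, the two agree.

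The sign grades below are assumed. The weights, area scores and thresholds are the protocol's.

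**Entry limit.** Area score 2 (10% to 29%) in every region:
- typical signs 2/2/1: 5 × 2 = 10
- worst-area signs 3/3/2: 8 × 2 = 16

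**Week 16, same patient, area score now 1 in every region:**
- typical signs 1/1/0: PASI 2, reduction 1 − 2/10 = 80.0%, responder
- worst-area signs 2/2/1 in all four regions: PASI 5, reduction 1 − 5/16 = 68.8%, non-responder
- worst-area signs 2/2/1 in the lower limbs only: 0.4 × 5 + 0.6 × 2 = 3.2, reduction 1 − 3.2/16 = 80.0%, still a responder

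**One residual 3/3/3 plaque.** Typical baseline signs are 3/3/3 with area score 3 in every region: 9 × 3 = 27. At Week 16 the area score is 2 and lesions are otherwise 1/1/1. Representative PASI is 3 × 2 = 6.0, a reduction of 77.8%. This assumes that the plaque is too small to move the average grade. By the worst-area rule, a plaque on the lower limbs gives 0.4 × 9 × 2 + 0.6 × 3 × 2 = 10.8; the other regions follow in the same way. The last column takes a baseline worst area of 4/4/4, so baseline is 12 × 3 = 36.

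| Region with the plaque | Week 16 PASI | Reduction from 27 (uniform baseline) | Reduction from 36 (mixed baseline) |
|---|---|---|---|
| Lower limbs | 10.8 | 60.0% | 70.0% |
| Trunk | 9.6 | 64.4% | 73.3% |
| Upper limbs | 8.4 | 68.9% | 76.7% |
| Head and neck | 7.2 | 73.3% | 80.0% |

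All four cases lose PASI 75 if baseline lesions were uniform. Only two do if the baseline was itself inflated by one grade.

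**The opposite direction.** Baseline worst area 4/4/4 and typical 3/3/3, area score 3: 36 against 27. At Week 16 lesions are uniform at 1/1/2 with area score 2, so PASI is 8.0 under both rules. The reduction is 1 − 8/36 = 77.8% (responder) by the worst-area rule and 1 − 8/27 = 70.4% (non-responder) by representative scoring.

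**The case against.** The strongest reply is that one rule applies to both blinded arms and at every visit, so much of the inflation may cancel in a percentage change, and nothing shows harm to the equivalence comparison. Most of this stands, and it limits what can be claimed.

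- **That one leftover plaque decides PASI 75.** A reader might infer this. It fails in the first Week 16 example (80.0% with one worst region), in two of the four mixed-baseline cases, and where one 3/3/3 plaque in a lower-limb region of area score 1 is the only disease left: 0.4 × 9 × 1 = 3.6, a reduction of 86.7% from 27.
- **That the rule admits ineligible patients.** PASI 10 against 16 does not establish this. Section 5.1 also requires BSA of at least 10% and sPGA of at least 3, and Appendix 3 ties sPGA 3 to moderate elevation and coarse scale over most lesions.
- **That the shift in response rate is known.** Simulations are possible only with invented inputs. One set (2 to 6 plaques per region, between-plaque SD 0.3 to 0.7) changed status in 5% to 19% of patients and moved the rate by about +1 to −19 points. Another (6 plaques per region, baseline SD 0.6) took PASI 75 from about 2% to 12% and gave it to under 1%. The protocol supports none of these inputs.
- **That the quoted originator rates (71.0% and 79.6%) do not carry over.** The sample-size assumptions are blacked out, and the protocol does not say how those studies scored severity.

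The wording may also be a loose translation. That does not remove the problem: as written, the sentence points to the most affected area, and no other text corrects it.

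**Conclusion.** The point holds as a defect in a stated measurement rule. Section 4.7.8 pairs worst-area severity with whole-region extent, so PASI is at least as high as a representative score and higher wherever lesions in a region differ. In the examples the difference is enough to cross the PASI limit of 12 and to change PASI 75 status, in either direction.

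The frequency and net direction cannot be settled from the protocol, because they depend on how lesions vary within regions at baseline and at Week 16. A reader might go further and infer that the primary comparison is biased towards one product, or that equivalence becomes easier to declare. The documents do not support this. The rule is common to both blinded arms, and any attenuation of the difference against the 0.15 margin would rest on assumed reclassification rates. The correction is worth making because it is specific and cheap and bears on the primary endpoint.

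**What to change.** Replace the sentence in section 4.7.8 with: *In each region, score each sign as its average severity over all psoriatic lesions of that region.* Put the same instruction on the PASI worksheet and in rater training, and apply one rule per patient from Week 0 to Week 55, so that baseline and Week 16 are always rated alike.

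The current text is Version 4.1, so rating may have started. In that case patients already rated by the worst-area rule keep it and are flagged, and the primary analysis is repeated by rating rule. If all patients have already been rated, keep the existing rule and report PASI 75 as based on worst-area severity, rather than mix two definitions in the primary endpoint.

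The cost is one sentence, a worksheet edit and a training note, plus one flag and one sensitivity analysis if the change comes after enrolment has begun.

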***Frequency and timing:***

The PASI and BSA are determined at screening, at Visit 1 (Week 0), Visit 4 (Week 5), Visit 6 (Week 9), Visit 8 (Week 13), Visit 10 (Week 16), Visit 13 (Week 21), Visit 15 (Week 24), Visit 18 (Week 29), Visit 20 (Week 33), Visit 22 (Week 37), Visit 26 (Week 45), and Visit 30 (Week 55).

**4.7.9. Static Physician Global Assessment (sPGA)**

The clinical course of psoriasis is assessed with the sPGA scale. The investigator chooses the sPGA item that best describes the patient’s symptoms. The scale is shown in Appendix 3.

The scale includes three criteria (induration, scaling, and erythema). Not all three criteria may be present. Induration is considered the most resistant symptom, while the presence of scaling or erythema can vary. In this case, the index is a sum of the scores for induration in the lesions and one of the prevailing criteria (erythema or scaling).

The investigator determines sPGA score at each visit and records it in the source documents and eCRF.

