### ***4.2. Description of the study type/design, study flow-chart, study procedures and periods***

#### ***Study design***

This clinical study of the efficacy and safety of BCD-057 and Humira® in patients with moderate-to-severe plaque psoriasis is a multicenter, double-blind, randomized, parallel-group study with an active comparator (Phase III).

The study will include 344 patients with definite moderate-to-severe plaque psoriasis diagnosed at least 6 months before signing the informed consent (the diagnosis should be confirmed by source documents). These patients should have the BSA of at least 10%, the PASI score of at least 12, and the sPGA score of at least 3.

Before enrollment, all patients will be given the full information about this clinical study, its purpose and the risks associated with study participation. After signing the informed consent form, the patient will undergo a screening examination (for not more than 4 weeks), which aims at confirming that the patient meets the study eligibility criteria. The Protocol does not provide any additional requirements regarding the diet or physical activity during the screening or study period.

According to the results of the screening exam, the investigator will make a decision whether to include the patient in the study or not. The patients who met the eligibility criteria were centrally randomized (with double blinding) into one of the study arms at a 1:1 ratio. At randomization, all enrolled patients were first stratified by body weight ( $< 80$  kg /  $\geq 81$  kg), prior use of antibodies for the treatment of psoriasis (experienced / naive), PASI score ( $< 20$  /  $\geq 20$ ), and presence of psoriatic arthritis (no / yes). Thus, after stratification, the arms will be balanced by all specified characteristics.

---

 Except for therapeutic monoclonal antibodies or their fragments that are specific for tumor necrosis factor alpha.

- Patients in Arm 1 (n = 172) will receive BCD-057 as SC injections given according to the following regimen: 80 mg on Day 1 of Week 0 followed by 40 mg on Day 1 of weeks 1, 3, 5, 7, 9, 11, 13, 15, 17, 19, 21, and 23.
- Patients in Arm 2 (n = 172) will receive Humira® as SC injections given according to the following regimen: 80 mg on Day 1 of Week 0 followed by 40 mg on Day 1 of weeks 1, 3, 5, 7, 9, 11, 13, 15, 17, 19, 21, and 23.

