**Appendix 3. Static Physicians Global Assessment (sPGA)**

| Score | Category    | Description                                                                                                                                                                                                                                                                     |
|-------|-------------|---------------------------------------------------------------------------------------------------------------------------------------------------------------------------------------------------------------------------------------------------------------------------------|
| 0     | Clear       | Plaque elevation = 0 (no elevation over normal skin)
Scaling = 0 (no scale)
Erythema = 0 (residual post-inflammatory hyper- or hypopigmentation)                                                                                                                          |
| 1     | Minimal     | Plaque elevation = +/- (possible but difficult to ascertain whether there is a slight elevation above normal skin)
Scaling = +/- (surface dryness with some white coloration)
Erythema = up to moderate (up to definite red coloration)                                   |
| 2     | Mild        | Plaque elevation = slight (slight but definite elevation, typically edges are indistinct or sloped)
Scaling = fine (fine scale partially or mostly covering lesions)
Erythema = up to moderate (up to definite red coloration)                                            |
| 3     | Moderate    | Plaque elevation = moderate (moderate elevation with rough or sloped edges)
Scaling = coarser (coarse scale covering most of all of the lesions)
Erythema = moderate (definite red coloration)                                                                            |
| 4     | Severe      | Plaque elevation = marked (marked elevation typically with hard or sharp edges)
Scaling = coarse (coarse, non-tenacious scale predominates covering most or all of the lesions)
Erythema = severe (very bright red coloration)                                            |
| 5     | Very severe | Plaque elevation = very marked (very marked elevation typically with hard sharp edges)
Scaling = very coarse (coarse, thick tenacious scale over most of all of the lesions; rough surface)
Erythema = very severe (extreme red coloration; dusky to deep red coloration) |

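### Section 4.7.9 gives two incompatible rules for scoring the sPGA, and the sum rule yields values off the Appendix 3 scale on which the entry and response cut-offs rest

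*Protocol*

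**What the plan says.** Section 4.7.9 opens with a selection rule: "The investigator chooses the sPGA item that best describes" the patient's symptoms, with the scale in Appendix 3. That appendix lists six mutually exclusive categories, 0 Clear, 1 Minimal, 2 Mild, 3 Moderate, 4 Severe and 5 Very severe. Each is worded for elevation, scaling and erythema together. The top category, for example, includes "Erythema = very severe (extreme red coloration; dusky to deep red coloration").

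The next paragraph of 4.7.9 names the three signs and notes "Not all three criteria may be present". It describes induration as the most persistent sign and the other two as variable, and then gives a second rule for this case: "the index is a sum of the scores for induration in the lesions and one of the prevailing criteria (erythema or scaling").

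Section 7.1.1 describes the instrument differently again: "This study uses the sPGA scale consisting of 5 questions".

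Two cut-offs use the score. Section 4.2 requires "the sPGA score of at least 3" together with PASI of at least 12 and BSA of at least 10%, and inclusion criterion 5 in Section 5.1 repeats this. Sections 4.1.2 and 7.1.2 define response as a score of 0 or 1 at Weeks 16, 24, 33 and 55. Neither place says which scoring rule applies.

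**The concern.** A category choice and a sum of two component grades have different ranges and meanings. If some patients are scored one way and some the other, a single variable holds values from two scales, yet it is read against one entry threshold and one response threshold.

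The condition attached to the sum makes this harder to manage. Treatment can remove a sign, so the rule could change within one patient between screening and Week 16.

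The protocol describes automatic eCRF calculation for PASI, NAPSI, DLQI and SF-36. For the sPGA it says only that the investigator determines and records the score, so nothing described would force one rule across sites.

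At stake are one of three joint entry criteria and a secondary endpoint assessed at four time points. Section 9.1 also lists the sPGA among the quantitative efficacy data, so mixed ranges would affect summaries of the score as well as the 0/1 proportion. Sections 1.5.1 and 7.1.3 rely on the sPGA, among other measures, because PASI alone may not suffice.

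**Working it through.** The protocol states no figure to reproduce. The check sets the two rules side by side and applies both to the same lesions.

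**Inputs**
- Rule A (4.7.9, first paragraph, with Appendix 3): score = the chosen category, 0 to 5.
- Rule B (4.7.9, second paragraph): score = induration grade + grade of the prevailing other sign (erythema or scaling), when not all three signs are present.
- Entry: score of at least 3 (4.2, 5.1). Response: score of 0 or 1 (4.1.2, 7.1.2).
- Component grades: **not in the protocol**, apart from the zeros in the Clear row. *Assumption:* each sign is graded 0 to 5 in step with the category numbers.

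**Range.** Rule A gives 0 to 5. Under the assumption, Rule B gives 0 + 0 = 0 up to 5 + 5 = 10.

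**Same lesions, both rules**

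| Lesions (induration + other sign) | Rule A | Rule B | Consequence |
|---|---|---|---|
| Clear, 0 + 0 | 0 | 0 | rules agree |
| Minimal, 0 + 1 | 1 | 1 | rules agree, responder |
| Minimal, 1 + 1 | 1 | 2 | responder under A, not under B |
| Minimal with moderate erythema, 1 + 3 | 1 | 4 | responder under A, not under B |
| Mild, 2 + 2 | 2 | 4 | fails the sPGA entry cut-off under A, meets it under B |
| Moderate, 3 + 3 | 3 | 6 | meets the cut-off under both |

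The fourth row is possible because Appendix 3 allows erythema up to moderate in category 1.

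**Dependence on the assumed grades.** If every visible sign is graded at least 1, induration plus one other sign gives at least 1 + 1 = 2. A score of 0 or 1 is then out of reach under Rule B whenever both are present. That direction does not need the exact 0-to-5 grading.

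**Ordering.** A patient with two signs at grade 2 and the third absent scores 2 + 2 = 4 by Rule B. A patient with all three signs at grade 2 scores 2 by Rule A. The patient with less disease gets the higher score.

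**Could a Mild patient meet the other entry criteria?** Use the PASI formula in 4.7.8 and assume the same grades (2, 2 and 0) in all four regions with area score 3 (30 to 49%):

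PASI = (2 + 2 + 0) × 3 × (0.1 + 0.3 + 0.2 + 0.4) = 4 × 3 × 1.0 = 12.

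This just reaches the PASI threshold, and BSA is well above 10%. With area score 2 the result is 4 × 2 = 8, which fails. Such a patient is possible but needs extensive involvement.

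**Number of patients affected.** This would require the distribution of component grades and the share of patients lacking a sign. The protocol gives neither, so no rate can be derived.

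**The case against.** The strongest case on the other side has four parts.

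1. The sum is a conditional fallback for patients who lack a sign, not the general rule. **This stands and limits the reach.** It does not remove the conflict, because the fallback still feeds values from another scale into the same variable and cut-offs.
2. A site cannot carry out the sum from the protocol, since Appendix 3 supplies no grades to add. The executable rule is therefore the category choice. The endpoint wording also attaches clearance to 0 and minimal disease to 1, matching the Appendix 3 labels. **This stands as evidence of what was probably intended.** It does not cancel a written instruction to raters, and no other passage overrides it. A site that follows it must invent its own grades.
3. Entry also needs PASI of at least 12 and BSA of at least 10%, so a Mild patient does not enter on the sPGA alone. **This stands.** The example above reaches PASI 12 only with 30 to 49% involvement in every region.
4. The primary endpoint, hypothesis and 0.15 margin concern PASI 75 at Week 16, and assessment is double-blind, so any misclassification should not differ by arm. **This stands and caps the severity.** Misclassification unrelated to arm would still tend to shrink a true difference in sPGA response, which is unhelpful in a comparison meant to support similarity.

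A reader might infer that nearly all category 1 patients would become non-responders, or that the sPGA response of 62.2% to 73.1% in Table 14 would be recorded at some specific lower rate. The protocol does not support either. The sum does not apply to every patient, some category 1 patients (0 + 1) keep a score of 1, and no distribution of grades is given.

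**Conclusion.** The point holds in a limited form and should be corrected. Section 4.7.9 contains two scoring rules that cannot both define one sPGA score. The second cannot be computed from the scale supplied and is off the scale to which the entry and response cut-offs belong. The five-questions description in 7.1.1 is a separate mismatch with Appendix 3. It creates no scoring rule of its own but adds to the confusion.

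The size is known only at patient level and rests on the assumption that component grades follow the category numbers. Under it, a 1 + 1 Minimal patient moves from 1 to 2 and loses response, and a 2 + 2 Mild patient moves from 2 to 4 and meets the sPGA part of entry. The number of such patients cannot be computed. The effect is confined to one entry criterion and a repeated secondary endpoint; the primary PASI 75 analysis does not use the sPGA.

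**What to change.** - In 4.7.9, delete the sentence that defines the index as a sum. State that the sPGA score is the single Appendix 3 category (0 to 5) that best fits the lesions overall, including when a sign is absent.
- State that this one score governs both the entry criterion (at least 3) and the responder endpoint (0 or 1).
- In 7.1.1, replace the five-questions description with a scale of six categories.
- Send the clarification to all sites.

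The cost is a few sentences and a site notice; design, sample size and visits do not change. Section 12.1 requires prior approval for amendments other than administrative ones, so the change may need that route. A notice cannot repair past data, so sites should be asked whether any recorded score was obtained by adding, and those scores should be checked against the source documents.
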